### Sample Size Determination

For sample size determination, we conducted a power calculation using the outcome of change in perceived risk of cigarette smoking from baseline to 2 months after each of the campaigns. The 8 study arms define a 2×2×2 analysis of variance (ANOVA) factorial design. Assuming a balanced design in each of the 8 study arms for the change in perceived risk, with n=70 per arm, we have at least 80% power to detect an effect size of 0.12 in a fixed-effects ANOVA. A total of 560 participants are needed to provide 70 participants per study arm at 2 months PC2, with complete measurements at baseline. We assume 11% attrition between the assessment at 7 days after the program and 2 months after the program and 1.5% attrition between baseline and the assessment at 2 months PC2 (ie, a total of 12.5% attrition). As a result, our retention rate is expected to be 87.5%. This assumes 640 participants randomized to 8 study arms. This sample size was calculated using PASS 2005 (NCSS, LP).

### Current Data Analysis

For the currently available baseline data, we used descriptive statistics to summarize sociodemographic characteristics (eg, age, gender, and race), tobacco-related characteristics (tobacco use and number of friends who use tobacco), and primary psychosocial health outcomes (ie, perceived risk of using each tobacco product).

Using the currently available data from the first weekly manipulation check survey, we checked to make sure that the message structures were perceived by participants as intended. Using one-way ANOVA, we examined study arm differences in perceived message loss framing, complexity level, emotional level, credibility, message enjoyment, perceived message relevance, and perceived message readability. STATA version 14 statistical software was used for data analysis.

### Planned Data Analysis

Once the trial is complete, we plan to conduct an exploratory analysis to identify which combination of message characteristics (ie, depth, framing, and appeal) most increases perceived risk of using each type of tobacco product. This analysis is exploratory because to date no theoretical framework or empirical evidence has been presented that demonstrates the importance of one message structure over another in the context of tobacco risk communication. We will first conduct, a series of 8 repeated-measures mixed-effects models for each type of tobacco product with the interaction effect (group [one combination vs all other combinations] × time [baseline, 2 months PC1, and 2 months PC2]) to predict perceived risk of using the product. These models will control for past 30-day use of the product at baseline and the crossover group assignment. In addition to the main outcomes analyses, we plan to conduct several moderation analyses, including the examination of different groups such as gender, race, mental health status, and personality types. This analysis will allow us to check if different types of individuals may respond differently to certain structures of text messages. Repeated-measures mixed-effect models with interaction effects will be conducted. For all data analysis, *P*<.05 is considered statistically significant. We will use STATA version 14 software (StataCorp LLC) for all analyses.

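### The stated 80% power comes from a 2×2×2 factorial ANOVA and is not tied to the planned one-combination-versus-the-rest models, which reach 80% only at about 0.36 SD and do not rank the combinations

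*Protocol article*

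**What the plan says.** Under Sample Size Determination the protocol article gives the basis for power: "The 8 study arms define a 2×2×2 analysis of variance (ANOVA) factorial design". The outcome is change in perceived risk of cigarettes from baseline to two months after the campaigns, and the claim is "with n=70 per arm, we have at least 80% power to detect an effect size of 0.12 in a fixed-effects ANOVA". The section does not say which effect in the ANOVA the 0.12 describes, or on what scale. It sets the number to be analysed at 560 and inflates this to 640 for 12.5% attrition.

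Under Planned Data Analysis the aim is to find which combination of depth, framing and appeal raises perceived risk the most. The method is "We will first conduct, a series of 8 repeated-measures mixed-effects models for each type of tobacco product with the interaction effect" of group by time, where group means "group [one combination vs all other combinations" and time has three levels. The models adjust for baseline past-30-day use and crossover group. P<.05 applies to all analyses, and the analysis is labelled exploratory. The article describes no model with framing, depth and appeal as factors and gives no power for the one-versus-rest contrasts.

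**The concern.** The two sections describe different analyses. A factorial term compares two halves of the sample. A one-versus-rest model compares an eighth of the sample with a pooled group of seven unlike arms, and three of those seven share any given feature with the arm under test. A real effect of one feature is therefore partly cancelled in the comparison.

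The contrast also does not match the question. Differing from the average of the other seven is not the same as being the best. Several arms can pass, and none of them need beat the runner-up. The article says the results would inform which messages go into larger campaigns, so a reader could take the 80% as applying to that choice when it does not.

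**Working it through.** **Inputs.** From Sample Size Determination: 70 per arm, N = 560, equal arms, effect size 0.12, power at least 80%. From Planned Data Analysis: eight contrasts per product and P<.05. Assumptions: 0.12 is Cohen's f; alpha 0.05 also applied to the power calculation; differences are in units of the SD of change, since no SD of change is given; the planned 2-df interaction is approximated by a 1-df comparison of change.

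**1. The plan's own figure.** Noncentral F, λ = N·f² = 560 × 0.12² = 8.064, denominator df 552.
- Numerator df 1: power 0.81. The stated figure reproduces.
- Numerator df 7 (omnibus test of eight arms): power 0.50. It does not reproduce.

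**2. What f = 0.12 means for each contrast.** For two groups with shares p and 1−p, f = d·√[p(1−p)].
- Factorial term, 280 vs 280: d = 0.12/0.5 = 0.24 SD.
- One versus rest, 70 vs 490: d = 0.12/√(1/8 × 7/8) = 0.12/0.331 = 0.363 SD.

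**3. Precision.**
- Factorial term: SE = √(1/280 + 1/280) = 0.0845.
- One versus rest: SE = √(1/70 + 1/490) = 0.1278.
- Variance ratio: (1/70 + 1/490)/(2/280) = 2.29.
- Difference detectable with 80% power (2.80 × SE): 0.237 SD against 0.358 SD.

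**4. One versus rest at 0.24 SD.** 0.24/0.1278 = 1.88, so power is about 0.47. The 2-df group-by-time test, under an assumed compound-symmetric correlation, gives 37% to 48% depending on how the effect is spread over the two follow-ups. Reaching 80% at 0.24 SD would take about 156 per arm, or 8 × 156 = 1,248.

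**5. When the truth is factorial.** Let each active factor shift the outcome by 0.24 SD (±0.12), additively. With k active factors the best arm lies 0.12k above the grand mean, and its distance from the other seven is 0.12k × 8/7.

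| Active factors | Arm minus rest (SD) | Divided by SE | Power for that arm |
|---|---|---|---|
| 1 | 0.137 | 1.07 | 0.19 |
| 2 | 0.274 | 2.15 | 0.57 |
| 3 | 0.411 | 3.22 | 0.90 |

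With one active factor, the first row applies to each of the four arms at the better level.

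**6. Best against next best.** 70 vs 70: 2.80 × √(2/70) = 0.47 SD for 80% power, before any adjustment for selecting the two arms.

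**7. Multiplicity.** With no true differences, the chance of at least one P<.05 among the eight contrasts is about 0.32 per product by simulation, allowing for their dependence. The independence value is 1 − 0.95⁸ = 0.34.

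**The case against.** Several stronger readings are tempting, and the article does not support them.

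- **That the 80% belongs to main effects, or reproduces only for a factorial term.** The sample size section names neither main effects nor a 0.24 SD difference. A single interaction term fits equally well. So does a one-versus-rest contrast at its own f = 0.12, which also has 0.81 power but then corresponds to 0.363 SD. The fair statement is that the powered effect is unspecified and that the same f means a larger raw difference in the planned contrast.
- **That the plan has only 19% power.** That is the chance for one named arm when exactly one factor acts. In the same case, the chance that at least one better-level arm is significantly above the rest is about 0.60. That comes at the price of the 0.32 false-positive chance when nothing differs.
- **That main effects must lead.** The stated question concerns combinations, and an author may reasonably keep it there.

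Two further defences carry some weight. The analysis is openly exploratory, with a reason given, and these models are described as coming first, so later models are not excluded. Repeated measures and covariates may also add precision. But the power calculation already uses change scores, no within-person correlation is given, and a factorial model could use the same repeated measures and covariates. The exploratory label softens the inference; it does not connect the two sections.

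**Conclusion.** The point holds in limited form. The stated power is not tied to the contrasts the article plans. At the 0.24 SD implied by a factorial term with f = 0.12, a one-versus-rest contrast has about 47% power, and it reaches 80% only at about 0.36 SD. How much is lost depends on the truth: a great deal if one factor acts, little or nothing if three act together. Separately, and whatever the power, one-versus-rest significance does not identify the combination that raises perceived risk the most.

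These figures assume that 0.12 is Cohen's f, that 70 per arm complete, that alpha is 0.05 per test, and that a 1-df comparison of change stands in for the planned interaction test. They do not show that the trial is too small for every plausible pattern of effects.

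**What to change.** For each product, fit one mixed model with framing, depth, appeal and all their interactions, each crossed with time, keeping the planned covariates. Report the factorial effects from it, since these are the basis of the sample size. Compare the eight model-based arm means with simultaneous intervals to rank the combinations. Keep the one-versus-rest contrasts as description only. Whether main effects or combination comparisons lead is the investigators' choice, but it should be stated.

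In the sample size section, say which effect the 0.12 refers to and on what scale, and add that one-versus-rest contrasts have 80% power only at about 0.36 SD.

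The cost is a short rewrite of the analysis plan and a less favourable stated detectable difference. No new data are needed, and there are fewer models to fit: one per product in place of eight. The article reports that outcome analysis was still to come, so the change could be made before results are seen.

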Enjoyment of messages (8-point scale)	5.90 (1.49)	5.87 (1.46)	5.78 (1.37)	6.13 (1.57)	5.93 (1.46)	5.93 (1.54)	5.78 (1.47)	5.96 (1.56)	5.80 (1.53)	.90
Perceived relevance (5-point scale)	2.37 (0.85)	2.37 (0.87)	2.40 (0.91)	2.38 (0.81)	2.57 (0.79)	2.22 (0.81)	2.41 (0.83)	2.26 (0.94)	2.40 (0.81)	.40
Perceived readability (5-point scale)	3.46 (0.78)	3.41 (0.81)	3.44 (0.84)	3.51 (0.75)	3.45 (0.85)	3.53 (0.70)	3.50 (0.75)	3.36 (0.84)	3.49 (0.71)	.93

^a^Missing values are not presented in this table. Out of 636 participants, 530 (530/636, 83.3%) completed the manipulation check survey.

^b^Participants were randomized to one of the 8 treatment arms, describing the type of messages.

^c^CGE: complex, gain-framed, emotional.

^d^CGR: complex, gain-framed, rational.

^e^CLE: complex, loss-framed, emotional.

^f^CLR: complex, loss-framed, rational.

^g^SGE: simple, gain-framed, emotional.

^h^SGR: simple, gain-framed, rational.

^i^SLE: simple, loss-framed, emotional.

^j^SLR: simple, loss-framed, rational.

^k^Significance testing with analysis of variance.

**Table 4 table4:** Baseline risk communication outcomes for the entire sample and by treatment arm.

Outcome^a^	Mean (SD)								
	Total	CGE^b^	CGR^c^	CLE^d^	CLR^e^	SGE^f^	SGR^g^	SLE^h^	SLR^i^
Perceived risk of using cigarettes	3.69 (0.55)	3.76 (0.49)	3.68 (0.52)	3.78 (0.35)	3.68 (0.6)	3.57 (0.65)	3.70 (0.56)	3.75 (0.47)	3.60 (0.63)
Perceived risk of using cigars	3.61 (0.56)	3.67 (0.49)	3.64 (0.5)	3.63 (0.52)	3.62 (0.56)	3.51 (0.62)	3.65 (0.56)	3.62 (0.54)	3.52 (0.67)
Perceived risk of using smokeless tobacco	3.48 (0.60)	3.49 (0.57)	3.44 (0.60)	3.59 (0.49)	3.47 (0.68)	3.45 (0.61)	3.48 (0.60)	3.56 (0.53)	3.38 (0.68)
Perceived risk of using hookah	3.09 (0.8)	3.00 (0.87)	3.15 (0.71)	3.37 (0.72)	3.09 (0.79)	2.99 (0.84)	3.13 (0.79)	3.11 (0.77)	3.01 (0.85)
Perceived risk of using e-cigarettes	3.06 (0.83)	2.98 (0.82)	3.17 (0.65)	3.31 (0.77)	3.08 (0.8)	2.98 (0.9)	3.11 (0.84)	3.04 (0.84)	2.96 (0.94)
Perceived personal benefits of e-cigarettes	0.88 (0.76)	0.87 (0.77)	0.88 (0.73)	1.02 (0.87)	0.76 (0.65)	0.91 (0.8)	0.85 (0.77)	0.89 (0.72)	0.85 (0.74)
Perceived general benefits of e-cigarettes	1.41 (0.69)	1.47 (0.51)	1.53 (0.68)	1.42 (0.69)	1.39 (0.72)	1.45 (0.78)	1.31 (0.77)	1.37 (0.73)	1.38 (0.64)
Perceived addictiveness of products	1.23 (0.59)	1.23 (0.53)	1.26 (0.56)	1.33 (0.59)	1.21 (0.64)	1.24 (0.55)	1.18 (0.62)	1.23 (0.61)	1.18 (0.61)

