## Discussion

### Overview

The Project Debunk trial will evaluate a comprehensive campaign delivered by mobile phone for increasing tobacco risk perception among a large sample of young adults in community college, including both tobacco users and nonusers. In particular, the trial will identify which structures of SMS text messages, if any, have the strongest effect on increasing the perceived risk of using conventional tobacco products and NETP. The results of this study will form the basis of an evidence-based resource that future researchers and practitioners could modify for use among their populations of interest.

To the best of our knowledge, this is the first published mHealth protocol for a trial that assesses the effect of a comprehensive and evidence-based mobile phone text messaging campaign for tobacco risk communication. This protocol summarizes the design and describes the planned evaluation of Project Debunk. Going beyond a simple presentation of our future study procedures, the protocol also presents the results from our baseline data. In particular, baseline information confirms that a substantial proportion of young adults at community colleges continue to smoke cigarettes, in addition to using NETP such as e-cigarettes and hookah. There were no differences among the treatment arms with respect to sociodemographic or tobacco-related characteristics. In addition, the treatment arms did not differ at the baseline with respect to the perceived risk of using any tobacco product. Preliminary results also show that we have successfully manipulated the 8-message structure combinations with our study sample. This is evident from treatment arm differences with respect to perceived message loss framing, emotional level, and complexity. All 8-message structure combinations were found to be enjoyable, easy to read, and credible.

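### The planned group × time models compare raw change from baseline, which loses precision and lets chance baseline imbalance tilt the ranking of message combinations

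*Protocol article*

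**What the plan says.** Planned Data Analysis sets out eight models per tobacco product. Each has an interaction of "group [one combination vs all other combinations"] with "time [baseline, 2 months PC1, and 2 months PC2]) to predict perceived risk of using the product". On adjustment it says: "These models will control for past 30-day use of the product at baseline and the crossover group assignment". Baseline perceived risk is not listed as a covariate, and nothing says that the arms share a common baseline mean. The aim is to find which combination "most increases perceived risk of using each type of tobacco product", and each test is read at *P*"<.05 is considered statistically significant".

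Sample Size Determination works on the same scale; its outcome is "change in perceived risk of cigarette smoking from baseline to 2 months after each of the campaigns".

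On baseline balance, Baseline Treatment Arm Differences in Outcome Measures reports no significant differences among the arms. The Discussion (Overview) goes further and says that "the treatment arms did not differ at the baseline with respect to the perceived risk of using any tobacco product".

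**The concern.** When baseline is a level of time and each group has its own baseline mean, the group × time terms equal the difference between groups in mean change from baseline. This has two consequences.

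- **Precision.** Unless baseline and follow-up are perfectly correlated, raw change is noisier than a comparison adjusted for baseline. The baseline score has already been collected, so the loss is avoidable.
- **Ranking.** An arm that starts high by chance regresses toward the mean and appears to gain less; an arm that starts low appears to gain more. The trial's question is which combination does best, so this bears directly on the answer.

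The statement that the arms did not differ could suggest that adjustment is unnecessary. But the absence of significance holds for the eight-arm comparison (7 degrees of freedom), whereas the planned tests set one arm against the other seven.

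**Working it through.** **1. The plan's own figure.** With 70 per arm (N=560), effect size 0.12 read as Cohen's f, a 1-df factorial effect, 552 error df and alpha 0.05, the noncentral F gives power 0.809. The stated 80% reproduces, and 560/0.875 = 640 reproduces the number randomized. The sample size is consistent with an analysis of change.

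**2. Is the interaction raw change?** The model was fitted to simulated complete data with both planned covariates. Its two interaction estimates (0.0942 and -0.1291) equalled the raw differences in mean change to four decimals. With 12.5% missing at PC2 the second estimate moved to -0.108, so the equality is exact for complete data and approximate under dropout.

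**3. Imbalance in the planned contrasts.** Means and SDs come from Table 4 (for example the row "Perceived risk of using hookah"). Arm sizes are back-calculated from the counts and percentages in Table 1: CGE 81, CGR 77, CLE 73, CLR 81, SGE 86, SGR 79, SLE 77, SLR 82, total 636.

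Hookah, CLE against the rest: the weighted mean of the other seven arms (n=563) is 3.067, so the difference is 3.37 - 3.067 = 0.303. The pooled SD is 0.796, SE = 0.796 × √(1/73 + 1/563) = 0.099, and t = 0.303/0.099 = 3.06.

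| Contrast at baseline | Difference | In SD | t | p | Eight-arm test |
|---|---|---|---|---|---|
| Hookah, CLE vs rest | +0.303 | 0.38 | 3.06 | 0.002 | F=1.83, p=0.08 |
| E-cigarettes, CLE vs rest | +0.266 | 0.32 | 2.59 | 0.010 | p=0.14 |
| Cigarettes, SGE vs rest | -0.136 | -0.25 | -2.15 | 0.03 | p=0.15 |

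**4. Expected shift given this imbalance.** Let rho be the baseline to follow-up correlation. It is not in the protocol, so a range is used. With equal variances at both times and no message effect, the expected difference in raw change is -(1 - rho) × baseline difference. For CLE on hookah:

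- rho 0.4: -0.6 × 0.303 = -0.18 points (0.23 baseline SD)
- rho 0.7: -0.3 × 0.303 = -0.09 points (0.11 baseline SD)

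**5. Compared with the detectable difference.** For one arm of 70 against 490, 80% power needs about 2.80 × √(1/70 + 1/490) = 0.36 SD of change. To use the same scale, divide the shift by √(2(1 - rho)). At rho 0.4: 0.229/1.095 = 0.209, which is 58% of 0.358. At rho 0.7: 0.114/0.775 = 0.148, which is 41%.

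**6. Effect on ranking.** Follow-up means were simulated with no message effect, given the Table 4 baselines (normal errors, baseline arm sizes, 200,000 replicates). By chance alone each rank has probability 0.125.

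| Result on raw change | rho 0.3 | rho 0.5 | rho 0.7 |
|---|---|---|---|
| CLE ranks last, hookah | 0.78 | 0.65 | 0.51 |
| CLE ranks last, e-cigarettes | 0.65 | 0.55 | 0.43 |
| SGE ranks first, cigarettes | 0.47 | 0.41 | 0.32 |
| CLE vs rest, hookah, rejects at 5% (single visit) | 43% | 31% | 20% |

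On raw change CLE ranks first for hookah with probability at most 0.01. With baseline adjustment its chances of ranking first or last are each about 0.13.

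**7. Precision.** For a single-visit contrast, variance with baseline adjustment divided by variance of change is (1 + rho)/2: 0.70 at rho 0.4 and 0.85 at rho 0.7, a cut of 30% to 15%. For the same raw difference, the 81% power of step 1 becomes about 94%, 91% and 87% at rho 0.3, 0.5 and 0.7. Put the other way, 70 × (1 + rho)/2, or about 46, 53 and 60 per arm, would match what 70 per arm give on change.

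**The case against.** The best defence is that the planned analysis is valid. Over repeated randomizations the change contrast is unbiased with a 5% type I error, and the stated power is on the change scale, so no planned power is lost. That is correct. The shift in step 4 is conditional on the imbalance that occurred; but that imbalance is now known, and the ranking will be read from this one allocation.

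The three contrasts are also selected. Of 40 baseline contrasts (eight arms, five products), 3 have p<0.05 where about 2 are expected, none survives a Bonferroni correction over 40, and the two CLE results come from the same participants. This rules out any claim of failed randomization. It does not remove the regression effect, which acts on chance imbalance.

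The article does not say outright that each group has its own baseline mean, and a model with a common baseline also treats baseline as a time level. The unconstrained reading is nevertheless the ordinary one, and it agrees with a sample size based on change.

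CLE also has the lowest past 30-day hookah use (11.0% against 18.2% overall), so part of its higher score may be a stable difference and regress less. That part is probably modest. The exploratory label lowers the stakes, but the result is meant to choose messages for a later intervention.

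**Conclusion.** The concern holds. As written, the main models compare raw change. Their validity over repeated randomizations is not in question; the problem is avoidable imprecision and a ranking tilted by baseline differences that can already be seen. CLE is disadvantaged for hookah and e-cigarettes, and SGE is favoured for cigarettes. For CLE on hookah the tilt is -0.18 to -0.09 points for rho between 0.4 and 0.7, roughly 58% to 41% of the detectable difference. The excess variance is 2/(1 + rho), or 1.43 to 1.18 times the adjusted variance.

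These sizes rest on an assumed rho, equal variances at both times, and baseline arm sizes rather than the participants eventually analysed. Both effects shrink as rho nears 1; neither changes direction for any rho below 1. No contrast for cigars or smokeless tobacco reached p<0.05. The Discussion's statement that the arms did not differ is supported only for the eight-arm tests.

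**What to change.** Change the model specification in Planned Data Analysis in one of two ways, and state it before the follow-up data are analysed (Status of Results shows that analysis as still to come):

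- keep the three-time mixed model but constrain the baseline mean to be equal across arms, as randomization justifies (constrained longitudinal data analysis); or
- take PC1 and PC2 as the outcome times, with baseline perceived risk of the same product as a covariate.

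Keep past 30-day use and crossover group in the model. In the Discussion, limit the balance statement to saying that the eight-arm tests were not significant.

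The cost is one line of specification and one reworded sentence. The data are already collected and the sample size need not change. The covariate version assumes a roughly linear relation between baseline and follow-up scores and needs a stated rule for missing baseline values; the constrained version handles those within the model.

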## Methods

### Study Design

Project Debunk has gathered data in the following 2 phases: (1) qualitative research for text message development and (2) a randomized trial. This research protocol briefly describes the methods used for the message-development phase and outlines the detailed information about the trial phase at baseline and 1 week after message exposure (ie, the intervention).

In design, the trial is being conducted as a 6-month-long randomized trial comparing 8 arms, based on the combination of the 3 message structures: framing, depth, and appeal (Figure 1). Participants are randomly assigned to one of the 8 arms. They are receiving text messages in 2 separate waves or campaigns. Each campaign consists of 2 text messages per day for 30 days (ie, 60 text messages). The 2 campaigns are 2 months and 1 week apart.

Allowing for a crossover design, participants within each of the 8 arms are randomly divided into 2 groups: group 1 is receiving text messages about conventional tobacco products during campaign 1 and then about NETP during campaign 2. Group 2 is receiving text messages about NETP during campaign 1 and then about conventional tobacco during campaign 2. This crossover design was advised by the Tobacco Center of Regulatory Science on Youth and Young Adults (TX TCORS) Scientific Steering Committee, as it will allow us to explore potential differences between the 2 categories of products within and between participants, with respect to their perceived risk of tobacco use. Data collection for the trial is being conducted at baseline, 2 months post campaign 1 (PC1), 2 months post campaign 2 (PC2), weekly throughout each campaign (a weekly manipulation check assessment), and 7 days after each campaign.

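### The product-specific models do not let the arm × time effect depend on which campaign carried the product, so the 2-month post-campaign-1 effect is diluted and the 80% power claim is unsupported there

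*Protocol article*

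**What the plan says.** Under Study Design, each of the 8 arms is randomly divided in two: "group 1 is receiving text messages about conventional tobacco products during campaign 1 and then about NETP during campaign 2". The second group has the reverse order. The split ratio is not given.

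Under Planned Data Analysis, a series of 8 models is fitted for each product. Each tests one message combination against the other seven, interacted with "time [baseline, 2 months PC1, and 2 months PC2]) to predict perceived risk of using the product". The adjustment set is stated: "These models will control for past 30-day use of the product at baseline and the crossover group assignment". No interaction of crossover group with time or arm is mentioned, and neither is an indicator of whether the product's own messages have yet been received.

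Under Sample Size Determination, power is computed "using the outcome of change in perceived risk of cigarette smoking from baseline to 2 months after each of the campaigns". The result is stated once for both campaigns: "with n=70 per arm, we have at least 80% power to detect an effect size of 0.12 in a fixed-effects ANOVA". The 70 per arm (560 in all) is required at the 2-month survey after campaign 2.

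**The concern.** The models are meant to show which message structure most raises the perceived risk of each product. At PC1, for any product that belongs to one category, one order group in every arm has had a full campaign about that category. The other has had a campaign about the other category only. A calendar-time arm × PC1 term averages the two.

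Listing crossover group as a control does not separate them. A main effect for order shifts all three waves equally, whereas the order difference should be absent at baseline, present at PC1 and different again at PC2. Even a crossover group × time term, which would absorb that pattern in the overall mean, leaves the arm × PC1 term as an average over exposed and unexposed participants. Only letting the arm effect vary with order, or with time-varying exposure, separates them.

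At stake is the reading of the PC1 result. A structure that works on the people who received the relevant messages would show a smaller effect, and a null PC1 result could be taken for an ineffective structure. The power statement offers no warning, because it applies the same effect size and the full 70 per arm after both campaigns.

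**Working it through.** **Inputs.** From Sample Size Determination: 70 per arm, N = 560, effect size 0.12 (read as Cohen's f), at least 80% power, and the design "The 8 study arms define a 2×2×2 analysis of variance (ANOVA) factorial design". From Planned Data Analysis: significance level 0.05, stated there for data analysis and assumed for the power calculation. From Study Design: two order groups per arm and the campaign timing. Assumed: a 1:1 split; 0.12 is the effect among those who have received the product's messages.

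**1. The plan's own figure.** Noncentral F with noncentrality N·f² = 560 × 0.12² = 8.06 and error df = 560 − 8 = 552.

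- Numerator df 1 (one main effect or interaction of the 2×2×2): power 80.9%. This reproduces the stated figure.
- Numerator df 7 (8-arm omnibus): 50.0%. This does not.

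The 80% is therefore for a 1-df factorial effect, that is, 280 against 280 with a standardized difference of 2 × 0.12 = 0.24 SD.

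**2. Dilution at PC1.** Let s be the share of the effect that the other category's messages produce (spill-over). Averaged over two equal order groups, the effect is multiplied by (1 + s)/2.

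| s | f at PC1 = 0.12(1 + s)/2 | Power, 1 df, N = 560 |
|---|---|---|
| 0 | 0.060 | 29.4% |
| 0.25 | 0.075 | 42.5% |
| 0.5 | 0.090 | 56.6% |
| 0.75 | 0.105 | 69.9% |
| 1 | 0.120 | 80.9% |

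At s = 0, about 2,184 evaluable participants would be needed for 80%. Using only the exposed half at PC1 (N = 280, f = 0.12) gives 51.6%.

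**3. PC2.** Everyone has had both message sets, so non-exposure dilutes nothing and 80.9% stands for the 1-df effect. Time since the product's own messages differs, however. It is about 2 months in the order group that received them second. In the other group it is 2 months + 1 week + the 30-day campaign + 2 months, about 61 + 7 + 30 + 61 = 159 days, or roughly 5 months.

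**4. Joint test of both changes.** For the same 1-df factorial effect with change scores correlated 0.5, the 2-df noncentrality is (280/2)·e′S⁻¹e, where e holds the two effects in SD of change and S is their correlation matrix.

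- Full effect at both waves, e = (0.24, 0.24): noncentrality 10.75, power 84%.
- Half at PC1 and full at PC2, e = (0.12, 0.24): noncentrality 8.06, power 72%.

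**5. The contrast actually planned.** One arm against seven is 70 against 490, with standard error √(1/70 + 1/490) = 0.128 SD. At 0.24 SD the power is 46.7%; 80% needs about 0.36 SD. If 0.36 SD is halved to 0.18 SD at PC1 (s = 0), power is 29%.

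**The case against.** The strongest reply is that the calendar-time model is legitimate. Order is randomized within every arm and so is independent of message structure. The arm × time term is then a fair order-averaged effect of being assigned a structure. That stands: a reader might infer that arms are unfairly compared, and the documents give no basis for it. But the stated aim is product-specific, and for that aim the PC1 average is diluted.

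A reader might also infer that the models ignore the crossover. They do not; they adjust for it. The exact coding may be settled in a fuller plan, and Study Design says the crossover is there to explore differences between product categories within and between participants. What remains is that the article fixes the interaction, the time coding and the adjustment set, and as worded these do not let the arm × time effect depend on order.

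Third, 29% is a worst case for one coefficient. It needs zero spill-over, although the not-yet-exposed group has already had 60 tobacco-risk texts of the same structure. The three-wave test loses less (84% to 72%), and the sample size is anchored at PC2. All of this stands, and it is why PC1 power is given as a range. If 0.12 were already the order-averaged effect, PC1 power would be as stated. With no spill-over, though, the effect among the exposed would then have to be 0.24, and the same 0.12 would not naturally apply at both surveys.

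Finally, the mapping from product to campaign is not clean everywhere. The Figure 1 legend places smokeless tobacco with conventional products and snus with the new products, while the description of the conventional messages does not list smokeless tobacco.

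**Conclusion.** The point holds for PC1. As worded, the arm × PC1 term mixes participants who have had the product category's messages with about half who have not. The 80% claimed for "change in perceived risk of cigarette smoking from baseline to 2 months after each of the campaigns" is therefore unsupported after the first campaign unless the other category's messages work about as well as the product's own. For a 1-df effect of f = 0.12 among the exposed, PC1 power is 29% to 81% over spill-over from none to full. This rests on a 1:1 split and on reading 0.12 as the effect among the exposed.

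It is tempting to extend the loss to PC2. The documents do not support a figure there: all participants are exposed, and any loss would depend on how fast the effect fades between about 2 and 5 months, for which they give no rate. It would also be wrong to say that the 80% simply carries over to an exposure-aligned version of the planned one-against-seven contrast; at 0.24 SD that contrast has about 47% power.

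This should be fixed but is not critical. The analysis is declared exploratory and no between-arm bias follows.

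**What to change.** In Planned Data Analysis:

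- Make the main contrast for each product the change from baseline to the 2-month survey after the campaign that carried that product (PC1 for one order group, PC2 for the other), using a time-varying exposure term, with crossover group × time terms for period.
- Report PC2 in the first-exposed group separately, as longer follow-up of about 5 months.
- Do not treat PC1 in the not-yet-exposed group as free of effect. Let arm × time vary by crossover group so that spill-over is estimated.
- State which campaign counts as the own campaign for smokeless tobacco.

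In Sample Size Determination:

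- Limit the 80% to a 1-df factorial effect (280 against 280) once all participants have received the product's messages.
- Give PC1 power as a range over spill-over, with the assumptions named.
- Do not attach 80% at f = 0.12 to the one-against-seven contrast. State that it has about 47% power at 0.24 SD and needs about 0.36 SD for 80%.

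The cost is a few extra model terms and a less favourable power statement. No new data are needed: Status of Results describes collection as underway and outcome analysis as still to come.
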